## Abstract

**Introduction::**

Chronic obstructive pulmonary disease (COPD) is commonly affected by particulate matter (PM) exposure. In this study, we aimed to evaluate whether behavioral interventions to reduce PM exposure improve clinical outcomes in patients with COPD.

**Methods::**

A multicenter randomized controlled trial will be conducted involving 120 participants recruited from 3 hospitals in the capital region of the Republic of Korea. Patients aged 40 to 80 years with a diagnosis of COPD and a forced expiratory volume at 1 s <80% of the predicted value are eligible for inclusion. The participants will be randomized to either the intervention group or the usual care group (2:1). The behavioral interventions will comprise the following activities: checking air quality forecast; operating indoor air cleaners and regular check-ups of filters; ventilating the home regularly by opening windows; adhering to inhaler treatment; and refraining from going out on high air pollution days. “Internet-of-things”-based, gravimetric, and light-scattering methods will be used to measure indoor and outdoor PM concentrations. To estimate the degree of individual PM exposure, a time-activity diary and land use regression modeling will be used. The efficacy of the behavioral interventions on the following outcomes will be analyzed: amount of PM exposure, changes in forced expiratory volume at 1 s from the baseline, changes in respiratory symptoms and quality of life, risks of exacerbation, hospitalization, and death.

**Discussion::**

Given the harmful effect of air pollutants, individual-level interventions to reduce exposure may be significant. However, there is a lack of evidence on how effective such interventions are to date. This study will be able to provide physicians and patients with evidence-based strategies to reduce PM exposure in daily life.

**Trial registration number::**

NCT04878367

## Introduction

1

Air pollution is undoubtedly a global public health issue with many facets. The World Health Organization estimated in 2016 that air pollution was responsible for 4.2 million premature deaths per year.^[1]^ Among various air pollutants, particulate matter (PM) has been recognized as a significant threat to public and individual health.^[2]^ PM is often classified by size fractions; PM_10_ and PM_2.5_ refer to particles with aerodynamic diameters of ≤10 μm and ≤2.5 μm, respectively. PM affects patients with chronic respiratory diseases by its penetrability into peripheral lung regions. Chronic obstructive pulmonary disease (COPD), the third leading cause of death worldwide,^[3,4]^ is one of the diseases that are commonly affected by PM exposure.^[5–8]^ According to a previous study, chronic exposure to ambient PM was associated with not only COPD morbidity but also with lower lung function.^[9]^ Ambient PM exposure was also linked to increased mortality,^[7,10]^ hospitalizations,^[6]^ and exacerbations,^[6,11]^ in patients with COPD.

Exposure to PM occurs not only outdoors but also in the indoor environment. Indoor air pollution has a wide range of impact on respiratory health; in particular, the development of COPD has been associated with air pollutants from indoor sources, such as solid fuel combustion and cooking.^[3,12,13]^ PM exposure in the indoor environment also affects the outcomes of COPD; Hansel et al^[14]^ have found that indoor PM_2.5_ concentrations in homes of former smokers with COPD were associated with an increased risk of severe exacerbations, increased burden of respiratory symptoms, and more frequent rescue medication use. As individuals spend majority of their time indoors, the health effects of PM should be evaluated considering air pollutant exposure not only outdoors but also in indoor environments.

Although hazardous outcomes of PM are recognized, evidence-based strategies for patient guidance are not concrete. There is a lack of research to date to support whether personal-level behavioral interventions to reduce PM exposure can improve clinical outcomes of patients with COPD. In a pilot study, the relationship between various daily behaviors aimed to reduce PM exposure and indoor/outdoor PM_2.5_ concentrations was investigated.^[15]^ The study found that a few behaviors, including checking air quality forecast and using an air cleaner, were associated with reduced indoor PM_2.5_ concentrations compared to outdoor concentrations. Based on the findings, we aim to evaluate whether the behavioral interventions and performances of certain protective measures in daily life improve clinical outcomes in patients with COPD.

## Methods

2

### Study design

2.1

This study is a multicenter randomized controlled trial evaluating the efficacy of behavioral interventions to reduce PM exposure in patients with COPD. A total of 120 patients will be enrolled from 3 academic institutions located in the capital region of the Republic of Korea (Fig. 1): 60 from Asan Medical Center (Seoul), 30 from Severance hospital (Seoul), and 30 from Ilsan Paik Hospital (Goyang). The study duration is 1 year and study participants will be followed up on every 3 months after a screening visit. This study was approved by the Institutional Review Board of each site: Asan Medical Center (2021-0701), Severance Hospital (4-2021-0607), and Ilsan Paik Hospital (2021-05-042). All of the participants will be asked to provide their written informed consent after receiving comprehensive information about the study. Additional informed consent will be obtained for the collection and use of biological specimens.

**Figure 1 F1:**
[figure not shown]
Study sites. Participants will be enrolled from 3 academic institutions located in the capital region of the Republic of Korea: Asan Medical Center (Seoul), Severance hospital (Seoul), and Ilsan Paik Hospital (Goyang). PM measuring devices will be installed and analyzed by the measuring team from Inha University Hospital. PM = particulate matter.

### Study participants

2.2

Patients who visit the outpatient clinics at each site will be screened for enrolment. The inclusion criteria of the study will be as follows: patients aged ≥40 years; those with a COPD diagnosis (postbronchodilator forced expiratory volume at 1 s [FEV_1_]/forced vital capacity <0.7); and those with FEV_1_ <80% of the predicted value. The following patients will be excluded: aged ≥80 years; have no respiratory symptoms; are unable to respond to questionnaires; or cannot understand air sampler device instructions.

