### Randomization and intervention

2.3

The study flow is shown in Figure 2. After enrolment, indoor PM_2.5_ concentrations will be measured for 1 month for each participant (baseline indoor PM_2.5_ concentrations). Study participants will be randomly allocated (1:1) either to the intervention group or the usual care group using the baseline monthly PM_2.5_ concentrations and baseline FEV_1_. The behavioral interventions will comprise the following 5 activities: checking the air quality forecast; operating an indoor air cleaner and regular check-up of filters; ventilating their home regularly by opening windows; adhering to inhaler treatment; and refraining from going out on high air pollution days. The intervention group will receive education at each visit on the importance of their behavioral change and will be advised to complete checklists everyday as part of their compliance with the interventions. Air cleaners will be rented to participants in the intervention group during the study period if they do not have one. The usual care group will continue to receive the treatment they were receiving but without any instructions on behavioral changes.

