### Data collection

2.4

The participants’ demographics and clinical data, including age, sex, body mass index, smoking status, medical history (including asthma), and exacerbation history will be obtained at enrolment. The participants will visit their respective hospitals every 3 months for 1 year. At each visit, the participants will perform pre- and postbronchodilator spirometry. Their COPD assessment test, modified Medical Research Council, and St. George Respiratory Questionnaire for patients with COPD scores will be obtained to assess respiratory symptoms and health-related quality of life. Development of acute exacerbation will be checked monthly via a telephone interview and/or at the regular follow-up visit. Any changes in inhaler medications or hospitalizations for respiratory causes will be monitored. Sputum samples will be obtained at each visit and blood samples, at the end of the study. The timeline of data collection is shown in Table 1.

**Table 1 T1:** Timeline of data collection.

	Screening	Visit 1	Visit 2	Visit 3	Visit 4
	0 mo	3 mo	6 mo	9 mo	12 mo
Clinical data					
PFT	+	+	+	+	+
CAT, mMRC	+	+	+	+	+
SGRQ	+	+	+	+	+
Exacerbation	Monthly				
Individual environmental risk assessment					
Residence	+				
Activity		+	+	+	+
Protective behavior	+	+	+	+	+
Indoor PM measurement					
Gravimetric method		+		+	
Light scattering method		+	+	+	+
Portable device		+	+	+	+
IoT-based device	Continuous monitoring				
Outdoor PM measurement					
IoT-based device	Continuous monitoring				
Air pollution network	Continuous monitoring				
Samples					
Sputum		+	+	+	+
Blood					+

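### Smoking may change during the year, but the article describes it as recorded at enrolment only, so a difference between arms could not be credited to the five behaviours and lower PM exposure

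*Protocol article*

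**What the plan says.** **Eligibility (section 2.2).** Inclusion rests on age, airflow obstruction, "and those with FEV_1_ <80% of the predicted value". The exclusions read: "The following patients will be excluded: aged ≥80 years; have no respiratory symptoms; are unable to respond to questionnaires; or cannot understand air sampler device" … Neither list mentions smoking by the patient or in the home.

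**Allocation (section 2.3).** Patients are allocated "using the baseline monthly PM_2.5_ concentrations and baseline FEV_1". Smoking is not named. The ratio is 1:1 in this section and 2:1 in the Abstract.

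**Collection (section 2.4, section 2.4.1, Table 1).** The time point for smoking status is entry to the study: "The participants’ demographics and clinical data, including age, sex, body mass index, smoking status, medical history (including asthma), and exacerbation history will be obtained at" that point. Indoor second-hand smoke is an item of the residential questionnaire, which is also completed at enrolment; Table 1 marks the residence assessment at screening only. Table 1 repeats activity and protective behaviour at Visits 1 to 4, but nothing describes either as covering smoking.

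**Intervention (section 2.3).** None of the five activities concerns smoking. Only the intervention arm receives education at each visit and a daily checklist.

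**Aim and analysis (sections 2.5 and 2.6, Figure 3 legend).** The trial asks whether the behaviours lower individual PM exposure and, through that, improve clinical outcomes. The tests named are t or Mann–Whitney and chi-squared or Fisher, with no covariate.

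**The concern.** The trial makes two claims: that the package changes outcomes, and that it does so because five named behaviours lower PM exposure. Smoking bears on the second. It can raise indoor PM, and it can affect lung function and symptoms by a route that PM monitors do not see. A fixed or portable monitor samples surrounding air, not the smoke a patient draws in. A home monitor also misses smoking that takes place elsewhere.

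Repeated teaching about clean air could lead a patient or relative to stop smoking, or to smoke outdoors. Indoor PM might then fall and symptoms or FEV1 might improve, with none of the five behaviours responsible. Year-round monitoring would show the fall in PM but not its cause. If smoking is not asked about after enrolment, no later analysis can recover the information.

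The population is also wider than that of one study the Introduction relies on, which found that "indoor PM_2.5_ concentrations in homes of former smokers with COPD were associated with an increased risk of severe exacerbations". That is a reason to look separately at non-smokers from smoke-free homes. It is not a reason to exclude anyone.

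**Working it through.** The article states no smoking prevalence, effect size, standard deviation or power, so there is no figure of its own to reproduce. The check has two parts.

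**1. What is controlled, and when**

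- Stable indoor smoking: partly controlled. It contributes to the one-month indoor PM2.5 measured before allocation and used in it.
- Past loss of lung function: largely controlled. Baseline FEV1 enters allocation, and the FEV1 outcome is the difference from baseline.
- Current smoking away from home, and inhaled smoke: balanced only in expectation, by randomisation.
- Change in smoking after allocation: not described as recorded. Outcomes are collected every three months and home PM all year, but no smoking item is shown after screening.

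**2. How much baseline smoking could matter**

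Inputs: N = 120 (section 2.1), split 60/60 (section 2.3) or 80/40 (Abstract). Alpha is 0.05 (section 2.6), taken as two-sided. Assumptions: smoking prevalence p of 10% to 40%, a smoker versus non-smoker difference d of 0.25 to 1.0 within-group SD, and 80% power.

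The standard error of the difference in smoker share is √[p(1−p)(1/n₁ + 1/n₂)]. At 60/60 this runs from √(0.09 × 2/60) = 5.5 points to √(0.24 × 2/60) = 8.9 points. At 80/40 it runs from 5.8 to 9.5 points.

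The chance that the arms differ by at least 10 points is an exact hypergeometric sum. With K = 120p smokers and x of them in arm 1, it adds C(n₁,x)·C(n₂,K−x)/C(120,K) over every x for which |x/n₁ − (K−x)/n₂| ≥ 0.10:

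| p | 60/60 | 80/40 |
|---|---|---|
| 10% | 0.125 | 0.102 |
| 20% | 0.254 | 0.225 |
| 30% | 0.319 | 0.291 |
| 40% | 0.352 | 0.323 |

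These figures ignore the allocation factors. They are upper values to the extent that balancing baseline PM2.5 also balances smoking.

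The shift in mean outcome from a 10-point imbalance is 0.10 × d, which is 0.025 SD (d = 0.25) to 0.10 SD (d = 1.0).

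The detectable difference is (1.960 + 0.842) × √(1−R²) × √(1/n₁ + 1/n₂), where R² is the share of outcome variance explained by smoking:

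| R² | 60/60 | 80/40 |
|---|---|---|
| 0 | 0.511 SD | 0.543 SD |
| 5% | 0.499 SD | 0.529 SD |
| 10% | 0.485 SD | 0.515 SD |
| 20% | 0.457 SD | 0.485 SD |

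Under the same assumptions R² = p(1−p)d²/[1 + p(1−p)d²] lies between 0.006 (p = 10%, d = 0.25) and 0.194 (p = 40%, d = 1.0). The shift is therefore about 5% (0.025/0.511) to 20% (0.10/0.511) of the detectable difference at 1:1, and adjustment recovers a modest amount of precision.

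**The case against.** The strongest reply is that the trial is randomised. Smoking is balanced in expectation, and quitting prompted by the education is a consequence of the assigned package, not a confounder of the arm comparison. That is right. A reader might infer that smoking is left uncontrolled or that it biases the comparison; the documents support neither.

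A reader might also try to put the imbalance in PM units. Suppose the PM2.5 SD in non-smoking homes is 10 µg/m³ and indoor smoking in 10% to 30% of homes adds 15 to 30 µg/m³. The 95% limit of imbalance at 60/60 is 1.96 × √(p(1−p) × 2/60) = 10.7 to 16.4 points, giving shifts of 0.107 × 15 = 1.6 to 0.164 × 30 = 4.9 µg/m³. This should not be read as an expected bias, for two reasons. First, the calculation assumes unrestricted allocation. On the same inputs indoor smoking accounts for 20.25/120.25 = 17% to 189/289 = 65% of between-home PM2.5 variance, and baseline PM2.5 is itself an allocation variable. Second, it is chance error already inside the standard error. At the upper end the total SD is √289 = 17, and the 95% range of the arm difference is ±1.96 × 17 × √(2/60) = ±6.1 µg/m³, of which the 4.9 is a component.

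Nor do the documents rank smoking as the largest competing source. They give no prevalence or source share, and the Introduction names solid fuel and cooking as indoor sources. Admitting smokers is a legitimate choice of population.

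Finally, this is a condensed article. The protective-behaviour form may already ask about smoking, and covariates may be set out in a plan not shown. If so, part of the point reduces to clarification. What stands is that the article gives an explicit collection schedule with no smoking item after screening, and analysis cannot repair data that were not collected.

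**Conclusion.** The point holds as one about attribution and data collection. As described, smoking is unrestricted at entry and recorded at enrolment only, so an arm-dependent change over the year would go unseen. The comparison by assigned group remains valid as the effect of the whole package. The further claim, that the five behaviours reduced individual PM exposure and thereby improved outcomes, would be hard to defend.

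The size of the unrecorded change cannot be calculated from the documents. The baseline part is modest: 0.025 to 0.10 SD for a 10-point imbalance, against a detectable difference of 0.511 SD (1:1) or 0.543 SD (2:1), resting on the assumed prevalence and smoker effect. The conclusion is the same under either allocation ratio, though the two stated ratios must be reconciled.

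**What to change.** 1. Ask about the patient's own smoking and smoking inside the home again at Visits 1 to 4, with the protective-behaviour questionnaire already scheduled then. Report the answers by arm. Use them to interpret the pathway, not as covariates in the main comparison, because they arise after randomisation.
2. Include baseline smoking (current smoker or smoking in the home, yes/no) as a covariate in the PM and clinical outcome models, if the full plan does not already do so.
3. Prespecify a sensitivity analysis in patients who at baseline do not smoke and live in smoke-free homes.

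A third allocation factor is not needed. With 120 patients at three sites, and PM2.5 and FEV1 already used, it risks thin strata for a small gain.

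The cost is two questions per visit; the covariate uses data already collected, and no patient is lost. The sensitivity analysis will be less precise. If 10% to 40% of patients fall outside it, 108 to 72 remain, and the detectable difference at equal arms is 2.802 × √(2/54) = 0.539 SD to 2.802 × √(2/36) = 0.660 SD. It should be read as supportive only.

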### Randomization and intervention

2.3

The study flow is shown in Figure 2. After enrolment, indoor PM_2.5_ concentrations will be measured for 1 month for each participant (baseline indoor PM_2.5_ concentrations). Study participants will be randomly allocated (1:1) either to the intervention group or the usual care group using the baseline monthly PM_2.5_ concentrations and baseline FEV_1_. The behavioral interventions will comprise the following 5 activities: checking the air quality forecast; operating an indoor air cleaner and regular check-up of filters; ventilating their home regularly by opening windows; adhering to inhaler treatment; and refraining from going out on high air pollution days. The intervention group will receive education at each visit on the importance of their behavioral change and will be advised to complete checklists everyday as part of their compliance with the interventions. Air cleaners will be rented to participants in the intervention group during the study period if they do not have one. The usual care group will continue to receive the treatment they were receiving but without any instructions on behavioral changes.

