### Study outcomes

2.5

We will investigate if the behavioral interventions reduce the degree of PM exposure and result in improved clinical outcomes compared with the usual care. The study outcomes are risks of acute exacerbation, respiratory-related hospitalization, death, difference in FEV_1_ from the baseline, and changes in the COPD assessment test, modified Medical Research Council, and St. George Respiratory Questionnaire for patients with COPD scores. The study concept is illustrated in Figure 3.

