### Statistical analysis

2.6

Data will be analyzed using SAS software (SAS Institute Inc., Cary, NC) and R software (version 3.5.2; R Development Core Team, Vienna, Austria). Data will be presented as means ± standard deviation or median [interquartile range] for continuous variables and percentages for categorical variables. The Student *t* test or Mann–Whitney test will be used for continuous variables, and the chi-squared test and Fisher exact test will used to compare categorical variables. *P*-values of <.05 will be considered of statistical significance. The risk of acute exacerbation and the incidence of respiratory hospitalization will be compared in the intervention group and the non-intervention group (Chi-squared test or Fisher exact test).

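### Allocation uses baseline PM2.5 and baseline FEV1 but the named tests adjust for neither, so the PM-exposure comparison is likely to be conservative and to lose power

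*Protocol article*

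**What the plan says.** Section 2.3 (Randomization and intervention) measures indoor PM2.5 in each home for one month before randomisation. Patients are then allocated "using the baseline monthly PM_2.5_ concentrations and baseline FEV_1". It does not say whether this means strata, minimisation or something else, and it gives no cut-points.

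Section 2.6 (Statistical analysis) names the tests. For continuous data: "The Student *t* test or Mann–Whitney test will be used for continuous variables". For categorical data it names chi-squared and Fisher exact tests, and it repeats them for two clinical outcomes: "The risk of acute exacerbation and the incidence of respiratory hospitalization will be compared in the intervention group and the non-intervention group". The threshold is "values of <.05 will be considered of statistical significance". No stratified or covariate-adjusted analysis is named, and the allocation factors do not appear.

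Section 2.5 (Study outcomes) defines the lung-function outcome as "difference in FEV_1_ from the baseline" and treats the three symptom and quality-of-life scores as changes. The last paragraph of the Discussion lists indoor PM concentrations among the between-group comparisons and does not describe them as a change from baseline.

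**The concern.** Balancing the arms on a prognostic factor removes that factor's contribution to the chance difference between arms. A two-sample test that does not know about the balancing still counts the factor as random error. Its standard error is then larger than the true sampling variability of the estimate, and its p-value is too large.

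This matters most for PM exposure. Reducing exposure is the step through which the intervention is meant to work, and one of the allocation factors is that outcome's own baseline. A substantial correlation is therefore plausible. The trial pays for a month of baseline measurement in every home, and the named tests do not use the precision it buys.

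**Working it through.** **Inputs from the article.** Total size: "A total of 120 patients will be enrolled from 3 academic institutions". Two allocation factors (section 2.3). Unadjusted tests at 0.05 (section 2.6), taken as two-sided because sidedness is not stated. No effect size, SD, correlation or power is given, so there is no power calculation to reproduce.

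**Assumptions.** Both factors are normal, independent and split at their medians. The outcome is a follow-up level with correlation r to baseline PM2.5, shown as a range.

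**Closed-form check (1:1, strata).**
- With unit outcome SD, the unadjusted test reports SE = 2/√120 = 0.183.
- A median split captures 2/π = 0.637 of a normal factor's variance. Balancing on it reduces the true variance of the difference by the factor 1 − 0.637r².
- Reported SE over true SD is k = 1/√(1 − 0.637r²), and true type I error ≈ 2Φ(−1.96k).

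| r | 1 − 0.637r² | k | type I error |
|---|---|---|---|
| 0.3 | 0.943 | 1.03 | 4.4% |
| 0.5 | 0.841 | 1.09 | 3.3% |
| 0.7 | 0.688 | 1.21 | 1.8% |

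**Simulation under the null, N = 120.** Each cell has 3,000 to 8,000 trials. At 3,000 trials the Monte Carlo standard error is √(0.05 × 0.95/3000) = 0.4 percentage points at a 5% rate.

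| Allocation | r = 0.3 | r = 0.5 | r = 0.7 |
|---|---|---|---|
| Strata, 1:1 | 4.8% | 3.8% | 1.9% |
| Strata, 2:1 | 4.5% | 3.9% | 2.2% |
| Minimisation, 90% | 4.6% | 4.0% | 1.7% |
| Minimisation, 85% (two runs) | 4.3%, 4.3% | 3.0%, 3.3% | 2.2%, 1.9% |
| Simple randomisation, 1:1 | 4.9% | 4.8% | 5.3% |

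In the strata 1:1 runs the ratio of reported SE to true SD was 1.03, 1.09 and 1.19, in line with k. ANCOVA on both factors gave 4.5% to 5.8% throughout, which is nominal within simulation error.

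**Precision.** In the strata 1:1 runs the ANCOVA and unadjusted SEs were 0.1745 and 0.1825 (r 0.3), 0.158 and 0.182 (r 0.5), and 0.1304 and 0.182 (r 0.7). Squaring the ratios gives 0.91, 0.75 and 0.51, against 1 − r² = 0.91, 0.75 and 0.51. The 85% minimisation runs gave 0.92, 0.76 and 0.51. These compare with the variance the unadjusted test *reports*. Against the *true* variance of the balanced unadjusted estimate the gain is smaller: (0.1735/0.1768)² = 0.96, (0.1587/0.1678)² = 0.89 and (0.1309/0.1535)² = 0.73. The rest of the loss comes from the overstated SE.

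**Power.** For an illustrative effect of 0.5 SD with strata 1:1, power rises with adjustment from 0.79 to 0.88 (r 0.5) and from 0.81 to 0.97 (r 0.7). With simple randomisation it rises from 0.77 to 0.88 and from 0.78 to 0.97.

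**Change scores.** With equal variances at both times, the correlation of change with baseline is −√((1 − r)/2). At r = 0.5 this is −0.5, so a change score is then distorted as much as a level. At r = 0.8, 0.9 and 0.95 it is −0.32, −0.22 and −0.16. Simulated type I error for FEV1 change at those values was 4.1%, 4.9% and 4.8%, with an SE ratio of 1.00 to 1.03.

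**Binary outcomes.** The chi-squared test, with about half of patients having the event, rejected in 5.0%, 5.8% and 3.8% of 4,000 trials at log-odds of 0.3, 0.5 and 1.0 per SD of each factor. Only the last is clearly below nominal.

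**The case against.** **Adjustment may be in an analysis plan that is not shown.** This is possible. But section 2.6 names its tests, so the point concerns a stated choice that does not fit the stated allocation. If another document adjusts, section 2.6 should be aligned with it.

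**The allocation mechanism and the correlations are not given.** This stands. Without balancing, the type I distortion disappears, as the simple-randomisation row shows, but the precision gain from adjustment remains. Across the assumed correlations the effect runs from trivial to marked.

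**The effect does not reach most outcomes.** This also stands. Baseline FEV1 already enters the FEV1 outcome by subtraction, and binary outcomes stay near nominal. For the symptom scores, neither allocation factor is the outcome's own baseline.

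A reader might infer more than the article supports:
- *That every planned comparison is wrong, or that false positives are inflated.* The first fails for the reasons just given. On the second, the error runs only in the conservative direction.
- *That the confidence intervals have the wrong coverage.* Section 2.6 states a p-value threshold and mentions no intervals.
- *That centre is wrongly left out of the allocation.* This would rest on the silence of a condensed article, which is not evidence of the trial's practice.

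The article also contradicts itself on the ratio: "Study participants will be randomly allocated (1:1) either to the intervention group or the usual care group" in section 2.3 against "The participants will be randomized to either the intervention group or the usual care group (2:1" in the Abstract. That is a separate matter, and the result here is much the same under either ratio.

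**Conclusion.** The point holds in a limited form. The named tests do not carry forward the two factors used in allocation. If those factors are balanced by strata or minimisation, the unadjusted comparison of follow-up indoor PM is conservative. Its true type I error is close to 5% at a correlation of 0.3, about 3–4% at 0.5 and about 2% at 0.7, with an avoidable loss of power. For FEV1 change the distortion is negligible. For binary outcomes it is small unless the factors are strongly prognostic.

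The direction of the error is certain once balancing is granted. Its size is not, because it depends on correlations and on an allocation mechanism that the article does not state, and on PM being analysed as a follow-up level. The validity of a positive result is not threatened. What is at stake is the chance of detecting a real effect with 120 patients.

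**What to change.** In section 2.6:

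- Analyse PM exposure and the other continuous outcomes by ANCOVA, with baseline monthly indoor PM2.5 (log scale) and baseline FEV1 as continuous covariates. For the symptom scores, add the score's own baseline.
- For exacerbation, use a regression or stratified test with the same two factors where event counts allow.
- Keep Fisher's exact test for sparse outcomes such as death, where a covariate model may not be estimable. The variance ratios above come from linear models and should not be carried over to these outcomes.

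In section 2.3, state how the two baseline values enter the allocation, so that the analysis can be matched to it.

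The cost is analysis wording and two or three degrees of freedom out of 120 patients. The baseline values are already collected.
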